# Assessment of Safety and Effectiveness of the Extracorporeal Continuous-Flow Ventricular Assist Device (BR16010) Use as a Bridge-to-Decision Therapy for Severe Heart Failure or Refractory Cardiogenic Shock: Study Protocol for Single-Arm Non-randomized, Uncontrolled, and Investigator-Initiated Clinical Trial

**DOI:** 10.1007/s10557-018-6796-8

**Published:** 2018-06-08

**Keywords:** Continous-flow ventricular assist device, Bridge to decision, Advanced heart failure, Investigator-initiated clinical trial

## Abstract

**Background:**

The management of heart failure patients presenting in a moribund state remains challenging, despite significant advances in the field of ventricular assist systems. Bridge to decision involves using temporary devices to stabilize the hemodynamic state of such patients while further assessment is performed and a decision can be made regarding patient management. The purpose of this study (NCVC-BTD_01, National Cerebral and Cardiovascular Center-Bridge to Dicision_01) is to assess the safety and effectiveness of the newly developed extracorporeal continuous-flow ventricular assist system employing a disposable centrifugal pump with a hydrodynamically levitated bearing (BR16010) use as a bridge-to-decision therapy for patients with severe heart failure or refractory cardiogenic shock.

**Method/Design:**

NCVC-BTD_01 is a single-center, single-arm, open-label, exploratory, medical device, investigator-initiated clinical study. It is conducted at the National Cerebral and Cardiovascular Center in Japan. A total of nine patients will be enrolled in the study. The study was planned using Simon’s minimax two-stage phase design. The primary endpoint is a composite of survival free of device-related serious adverse events and complications during device support. For left ventricular assistance, withdrawal of a trial device due to cardiac function recovery or exchange to other ventricular assist devices (VADs) for the purpose of bridge to transplantation (BTT) during 30 days after implantation will be considered study successes. For right ventricular assistance, withdrawal of tal device due to right ventricular function recovery within 30 days after implantation will be considered a study success. Secondary objectives include changes in brain natriuretic peptide levels (7 days after implantation of a trial device and the day of withdrawal of a trial device), period of mechanical ventricular support, changes in left ventricular ejection fraction (7 days after implantation of a trial device and the day of withdrawal of a trial device), and changes in left ventricular diastolic dimension (7 days after implantation of a trial device and the day of withdrawal of a trial device).

**Ethics and Dissemination:**

We will disseminate the findings through regional, national, and international conferences and through peer-reviewed journals.

**Trial Registration:**

UMIN Clinical Trials Registry (UMIN-CTR; R000033243) registered on 8 September 2017.

## Background

Implantation of ventricular assist devices (VADs) has become an indispensable alternative for the treatment of patients with severe end-stage heart failure [1–3]. However, despite recent advancements in the field of VADs, the outcome remains poor for patients classified as interagency registry for mechanically assisted circulatory support (INTERMACS) profile 1 especially with severe respiratory, renal, and hepatic failure [4]. Patients with serious low cardiac output syndrome require an adequate amount of blood flow to recover from severe multi-organ failure. The use of temporary devices such as extracorporeal VAD provides a solution to establish adequate blood flow and stabilize the hemodynamic state of the patients while further assessment of the clinical condition is being performed and a process referred to as bridge to decision (BTD), when it is unclear whether the patient’s heart will recover or whether the patient will need alternative, longer-term therapy or transplantation [5–8]. In terms of cost-effectiveness, an extracorporeal continuous-flow VAD that uses a disposable pump is desirable for BTD [9]. Recently, some clinicians have reported using a conventional disposable centrifugal pump and a cannula for cardiopulmonary bypass (CPB) for BTD [10, 11]. However, in conventional pumps with contact bearings, thrombus formation occurs within just a few days because of blood cell destruction and blood coagulation caused by mechanical wear and heat generation. A blood pump system with longer durability and superior hemocompatibility than conventional pump for cardiopulmonary bypass, and lower cost than implantable VADs is required that is able to provide enough time for decision-making without the risk of system replacement or system-related complications. Recent developments in the field of blood pumps have focused on noncontact bearing systems with hydrodynamically or magnetically levitated bearings, which have demonstrated excellent blood compatibility and low hemolytic effect, ensuring long-term durability of the VADs [12–15]. As regards an implantable left VAD (LVAD), HeartMate 3 LVAD was invented as a fully magnetically levitated centrifugal-flow chronic LVAD and Netuka et al. [15] showed that HeartMate 3 was safe, with high 30-day and 6-month survival rates, a favorable adverse event profile, and improved quality of life and functional status. The prospective, randomized Multicenter Study of MagLev Technology in Patients Undergoing Mechanical Circulatory Support Therapy with HeartMate 3 (MOMENTUM 3) clinical trial has been carried out to evaluate the safety and effectiveness of the HeartMate 3 LVAD by demonstrating non-inferiority to the HeartMate II LVAD (also St. Jude Medical, Inc.) [16].

As regards extracorporeal VAD, there is no approved centrifugal-flow pump for LVAD use in the world. The Levitronix® CentriMag® ventricular assist system (VAS) (Levitronix LLC; Waltham, MA) is a magnetically levitated centrifugal-flow pump that can be clinically applied as LVAD and right VAD (RVAD) in USA [6, 8]. Although the Levitronix CentriMag is authorized by federal law to provide temporary circulatory support for up to 30 days for patients in cardiogenic shock due to acute right ventricular failure, the effectiveness of this device for this use has not been demonstrated and distribution of this device is restricted to use by or on the order of a physician. When used for left or biventricular support for periods over 6 h, the CentriMag VAS is an investigational device limited by federal (USA) law to investigational use. This device will be used for up to 30 days to support one or both sides of the heart as a bridge to decision, when it is unclear whether the patient’s heart will recover or whether the patient will need alternative, longer-term therapy or transplantation. This prospective, non-randomized trial will enroll a total of 30 patients at up to 25 clinical centers. The CentriMag Pivotal Trial will be conducted jointly by Thoratec and Levitronix.

The core components of the CentriMag VAS consist of a continuous-flow centrifugal blood pump, a primary console and motor, a flow probe, a backup console and motor, a tubing, and cannulas. The pump, which has a priming volume of 31 mL, can be operated up to a maximum speed of 5500 rpm while generating up to 9.9 L/min flow [17]. When the pump is inserted into the motor and activated, the internal impeller is electromagnetically levitated and centered, eliminating the need for shafts, seals, and bearings in the pump. Shafts, seals, and bearings are the sites typically responsible for hemolysis, thrombus, and particle formation. Large gaps between the impeller and the pump housing are designed to minimize potential shear forces on blood cells, thereby allowing high blood flow rate with minimal hemolysis. Utilizing magnetic levitation to suspend and spin the impeller reduces friction in the pump and eliminates the point source of friction (bearing) resulting in minimal heat and wear of the pump components.

Our center developed a new extracorporeal continuous-flow temporary LVAD that uses a novel disposable centrifugal blood pump with a hydrodynamically levitated bearing (HLB). As ensuring the performance and safety of the VAD as a whole is important, the combination of the pump, cannulas, connectors, and circuits was well designed. An HLB utilizes hydrodynamic pressure at the small gaps between the rotating part (the impeller) and the stationary part (the casing wall) to counter mechanical loads, and this pressure, in a general sense, is dependent on the rotational speed (RS). There remains a possibility of mechanical contact between the rotating part and the stationary part when the blood pump is operated at a low speed. The effectiveness and safety of the pump in the setting of extracorporeal membrane oxygenation have been reported [18], in which the afterload of the blood pump is assumed to be higher than that in LVAD cases because of small cannula diameters and the hydraulic resistance of oxygenators. In the goat model, this newly developed temporary LVAD demonstrated consistent and satisfactory hemodynamic performance and hemocompatibility over the course of a 30-day experiment [19]. The outcomes of this previous study have served to establish the optimal composition and design of our new LVAD for BTD and this newly developed LVAD represents a promising tool for BTD in critically ill patients.

The purpose of this study (NCVC-BTD_01, National Cerebral and Cardiovascular Center-Bridge to Dicision_01) is to assess the safety and effectiveness of the extracorporeal continuous-flow VAD (BR16010) use as a bridge-to-decision therapy for patients with severe heart failure or refractory cardiogenic shock.

## Methods and Analysis

### Study Design

NCVC-BTD_01 is a single-center, single-arm, open-label, exploratory, medical device, investigator-initiated clinical study. It is conducted at the National Cerebral and Cardiovascular Center in Japan.

### Study Period

Enrollment of study participants started in October 2017 and will end in July 2018; then, results of this study will be published.

### Sample Size

A total of nine patients will be enrolled in the study. The study was planned using Simon’s minimax two-stage phase design [20]. The hypothesis to be tested was H0: P < P0 vs H1: P > P1, where P is the probability of mortality at 30 days, accepting a false-positive rate (*α*) ≤ 10% and a false-negative rate (*β*) ≤ 10%, and P0 was set to 50% and P1 was set to 90%. These parameters lead to a two-stage design with the first stage of four patients stopping if two or fewer survive, or continuing accrual to a total of nine patients, declaring success if more than seven patients survive.

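### The final success cut-off is one patient too strict for the stated error rates: more than seven of nine gives 77.5% power, not 90% or more

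*Protocol article*

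**What the plan says.** All the design inputs are in the Sample Size section of the protocol article:

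- Method: "The study was planned using Simon’s minimax two-stage phase design".
- Rates: "P0 was set to 50% and P1 was set to 90" per cent.
- Error limits: "accepting a false-positive rate (*α*) ≤ 10" per cent and "a false-negative rate (*β*) ≤ 10" per cent.
- Stage 1: "the first stage of four patients stopping if two or fewer survive".
- Final rule, after continuing to nine patients: "declaring success if more than seven patients survive".

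The section presents the two-stage rule as the result of those parameters. No other part of the article gives a different cut-off.

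**The concern.** A Simon design is fully determined by the two rates, the two error limits and the choice of minimax or optimal, so the claim that these inputs lead to this rule can be checked exactly. In Simon's usual notation the rule as written is 2/4 and 7/9: stop at two or fewer of four, and reject the device at seven or fewer of nine. Eight of nine is 89% observed survival. A device whose true survival is exactly the 90% target would often fall short of that, so power of 90% looked implausible.

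This is the only success criterion the article states with a numerical threshold. If it does not have the stated properties, a result of seven out of nine is ambiguous: a failure under the written rule, but a success under the design that meets the stated error rates.

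**Working it through.** **Inputs** (all from Sample Size): p0 = 0.50, p1 = 0.90, α ≤ 0.10, β ≤ 0.10, n1 = 4, r1 = 2, N = 9, success if more than r = 7 survive.

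**Reading of P.** The section says "where P is the probability of mortality at 30 days". Both decision rules count survivors and more survivors favour the device, so P is taken here as 30-day survival. The mortality wording is a separate slip and does not affect the arithmetic.

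**Formula.** With X1 ~ Bin(4, p) and X2 ~ Bin(5, p),

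P(success) = Σ over x1 = 3, 4 of P(X1 = x1) × P(X2 ≥ r + 1 − x1).

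**Building blocks**

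| | p = 0.5 | p = 0.9 |
|---|---|---|
| P(X1 = 3) | 0.2500 | 0.2916 |
| P(X1 = 4) | 0.0625 | 0.6561 |
| P(X2 = 5) | 0.03125 | 0.59049 |
| P(X2 ≥ 4) | 0.18750 | 0.91854 |
| P(X2 ≥ 3) | 0.50000 | 0.99144 |

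**Rule as written (more than seven, i.e. at least 8 of 9)**

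- α = 0.2500 × 0.03125 + 0.0625 × 0.18750 = 0.0078 + 0.0117 = 0.0195
- Power = 0.2916 × 0.59049 + 0.6561 × 0.91854 = 0.1722 + 0.6027 = 0.7748
- β = 1 − 0.7748 = 0.2252, against a limit of 0.10

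**One patient lower (more than six, i.e. at least 7 of 9)**

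- α = 0.2500 × 0.18750 + 0.0625 × 0.50000 = 0.0469 + 0.0313 = 0.0781
- Power = 0.2916 × 0.91854 + 0.6561 × 0.99144 = 0.2678 + 0.6505 = 0.9183

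Both limits are met.

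**Can another stage 1 rule rescue the written cut-off?** No. A futility stop can only lose power, and a single-stage test requiring 8 of 9 already has power 0.9⁹ + 9 × 0.9⁸ × 0.1 = 0.7748. The figure equals the two-stage one because eight or more of nine forces at least three of the first four.

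**Full enumeration** of two-stage designs under the stated limits: none with N below 9 qualifies, and every qualifying design with N = 9 has r = 6. Among these, 2/4 with 6/9 has the smallest expected size under p0:

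- Probability of early stopping = 1 − 0.2500 − 0.0625 = 0.6875
- Expected N = 4 + 5 × 0.3125 = 5.56

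It is therefore the minimax design. The article's n1, r1 and N match it exactly; only the final cut-off differs.

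**Do other error limits give 2/4 and 7/9?** The pairs (α, β) = (0.05, 0.10), (0.10, 0.20), (0.05, 0.20), (0.025, 0.20) and (0.05, 0.25) were tried, and none returns it as the minimax design. The pair (0.05, 0.10) returns 2/4 and 7/**10** (α 0.0488, power 0.9040), which has the same stage 1 and the same r but ten patients.

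**Trials affected.** At p = 0.9, the probability of passing stage 1 and ending with exactly seven survivors is 0.9183 − 0.7748 = 0.1435.

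**The case against.** The arithmetic is not in dispute; the case against concerns its weight and the remedy.

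- **The error is conservative.** True: the false-positive rate is 1.95% against an allowed 10%, so an ineffective device gains nothing. The section also commits to a false-negative limit, however, and the rule exceeds it more than twofold.
- **The study is exploratory and the Statistical Analysis section is descriptive.** True, and the article names no action that follows from declaring success. It still states a hypothesis, error rates and a success rule, and these must agree.
- **The stage 1 rule still works under the written cut-off.** This stands. It changes neither α nor power, but it stops 68.75% of trials under p0 and reduces expected size to 5.56, exactly as under the lower cut-off.
- **Seven of nine is weak evidence.** The Statistical Analysis section plans exact two-sided 95% intervals. The lower limit is about 0.40 for 7/9, which leaves 50% inside the interval, and about 0.52 for 8/9, which excludes it. So a success at 7/9 could be reported beside an interval covering p0. That follows from choosing a 10% error limit and does not make the written rule consistent with its inputs, but the sponsor should know it.
- **The threshold would be relaxed mid-trial.** Four patients had been enrolled by the end of January 2018 in an open-label, single-centre study. This stands, and it affects how the correction should be made.

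**Conclusion.** The concern holds. With the stated inputs, the written rule has power 77.5%, which is 12.5 points below the promised minimum of 90% and 14.3 points below the 91.8% of the matching minimax design. The false-negative rate is 22.5% instead of at most 10%. The type I error is not inflated.

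The conclusion rests on reading P as survival, which the survivor counts require, and on exact binomial probabilities with all nine patients evaluable.

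Because n1, r1 and N all reproduce, the likeliest explanation is a wording slip of more than seven for seven or more. The article alone cannot prove that. The 7/10 design at α = 5% shows another way a seven could have entered the text.

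**What to change.** Check the original design output and the approved protocol, then do one of the following:

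1. **If the intended design was 2/4 and 6/9**, state that success is declared when seven or more of nine patients survive. Give the exact properties: α 7.8%, power 91.8%, 69% probability of early stopping under p0, expected size 5.6 under p0.
2. **If eight or more of nine is intended**, keep it, restate the design as α 2.0% and power 77.5%, and drop both the claim that β is at most 10% and the claim that the stated parameters lead to this rule.

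Neither option adds patients. The first raises the false-positive rate from 2.0% to 7.8%, still within the stated 10%, and permits a success whose 95% interval includes 50%. The second accepts a 22.5% chance of missing a device at the target rate.

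The text change is one or two sentences in a documented amendment. Because the trial is open-label and its first four patients are already enrolled, the amendment should cite the original design evidence and be dated before final outcomes are known. Otherwise a move from eight to seven would look data-driven. The same amendment should correct the definition of P from mortality to survival.

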### Study Objectives and Endpoints

The primary objective of this first-in-human trial (NCVC-BTD_01) is to assess the safety and effectiveness of the BR16010 to support one or both sides of the heart as a BTD VAD for patients with severe heart failure or refractory cardiogenic shock refractory to optimal medical management, standard surgical procedures, or mechanical circulatory supports [e.g., intra-aortic balloon pumping (IABP), ventriculo-arterial bypass (VA bypass), and percutaneous cardiopulmonary support (PCPS)]. The study had a single set of entry criteria for patients designated for bridge to recovery (BTR) or bridge to transplantation (BTT).

The primary endpoint is a composite of survival free of device-related serious adverse events and complications during device support. For left ventricular assistance, withdrawal of a trial device due to cardiac function recovery or exchange to other VADs for the purpose of BTT during 30 days after implantation will be considered study successes. For right ventricular assistance, withdrawal of trial device due to right ventricular function recovery within 30 days after implantation will be considered a study success.

Secondary endpoints include changes in brain natriuretic peptide (BNP) levels (7 days after implantation of a trial device and the day of withdrawal of a trial device), period of mechanical ventricular support, changes in left ventricular ejection fraction (LVEF) (7 days after implantation of a trial device and the day of withdrawal of a trial device), and changes in left ventricular diastolic dimension (LVDd) (7 days after implantation of a trial device and the day of withdrawal of a trial device).

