(4) Evidence of irreversible intrinsic respiratory disease (e.g., chronic pulmonary disease, acute respiratory distress syndrome) which needs mechanical respiratory support (except when the primary investigator deems it as a sign of acute heart failure)	
(5) Contraindicated for anticoagulation	
(6) Difficulty of 30-day observation is anticipated	
(7) Pregnant or suspected pregnant at time of study entry	
(8) Participating in another clinical trial at time of study entry	
(9) Deemed unsuitable by the primary investigator for other reasons	

The trial VAD is implanted within 3 days after study entry. Patients were followed to the primary endpoint at 30 days after implantation of trial VAD or other outcomes (transplant, explant, or death), whichever occurred first. Patients will be followed for 7 days after removal or until other outcomes. For enhancing patient safety, the enrollment is held after the fourth patient is registered until the independent safety board confirms the 7-day safety for the patients. A summary of the study design is shown in Fig. 3. The schedule of data to be collected is presented in Table 2.

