**Fig. 3 Fig3:**
[figure not shown]
Summary of the study design

**Table 2 Tab2:** Data to be collected as part to of this study

Variables	Screening (baseline)	1–7 days	14 days	21 days	30 days	Every 2 weeks after 30 days	At VAD removal	7 days after removal
Patient information								
Basic characteristics	○							
Vital signs	○	○	○	○	○	○	○	
Image examinations								
Electrocardiogram	○	○	○	○	○	○	○	
Ultra sound cardiography	○	○	○					
Chest X-ray	○							
Brain CT scan	○							
Blood examinations								
Blood cell counts, electrolytes, chemistry, coagulation, etc.	○	○	○	○	○	○	○	
Heart function								
NYHA classification (or Ross classification)	○	○	○					

*CT* computer tomography, *NYHA* New York Heart Association

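### The primary endpoint window closes at device removal, so device-related events in the planned 7 days afterwards are not scored, and it conflicts with the 30-day definitions elsewhere in the protocol

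*Protocol article*

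**What the plan says.** Four places in the protocol article bear on what is scored and when.

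- **Study Objectives and Endpoints, composite:** "The primary endpoint is a composite of survival free of device-related serious adverse events and complications during device support".
- **Same section, success routes:** for left-sided support, "withdrawal of a trial device due to cardiac function recovery or exchange to other VADs for the purpose of BTT during 30 days after implantation"; for right-sided support, "withdrawal of trial device due to right ventricular function recovery within 30 days after implantation will be considered a study success". Neither route carries a condition on the patient's state after removal.
- **Patient Enrollment and Study Schedule:** "Patients were followed to the primary endpoint at 30 days after implantation of trial VAD or other outcomes (transplant, explant, or death), whichever occurred first". Shortly afterwards: "Patients will be followed for 7 days after removal or until other outcomes". Nothing ties this second period to the endpoint. Table 2 has a data column headed "Every 2 weeks after 30 days", so support past day 30 is foreseen.
- **Sample Size:** the tested quantity is described with the words "where P is the probability of mortality at 30 days". The decision rule counts survivors: stop if two or fewer of the first four survive, and declare success if more than seven of nine survive.

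**The concern.** Removal for recovery is the only success route for right-sided support and one of two for left-sided support. Whether the recovery holds is the evidence that the removal was justified. With the window closed at removal, that evidence is gathered in the planned 7 days but cannot change the score.

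The investigators also choose the removal date, in a single-arm, open-label study. The same clinical decision ends the time at risk for a counted event and triggers success.

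At the other end, the sections disagree on whether the endpoint is settled at day 30 or runs for as long as support lasts. With nine patients, a single patient whose status depends on which section is read can move the result.

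**Working it through.** **The plan's own figure.** Inputs from Sample Size: P0 = 0.50, P1 = 0.90, α ≤ 0.10, β ≤ 0.10, first stage 4 patients (stop at 2 or fewer), total 9. The chance of declaring success with more than r of nine is

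Σ (x = 3, 4) C(4,x) pˣ(1−p)⁴⁻ˣ × P(Bin(5,p) ≥ r+1−x).

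- r = 6, p = 0.5: 0.25 × 6/32 + 0.0625 × 16/32 = 0.078.
- r = 6, p = 0.9: 0.2916 × 0.9185 + 0.6561 × 0.9914 = 0.918.
- r = 7 (as printed), p = 0.5: 0.25 × 1/32 + 0.0625 × 6/32 = 0.020.
- r = 7, p = 0.9: 0.2916 × 0.5905 + 0.6561 × 0.9185 = 0.775.

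Enumerating all two-stage designs up to 15 patients reproduces the total of 9, the first stage of 4 and its stopping limit as the minimax design, but with success at more than six. The printed cut-off misses the stated β. That is a separate matter. What counts here is that this rule is about survival, not about the composite.

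**The definitions side by side.** The patients are hypothetical and the days are chosen only to separate the definitions.

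| Patient | Composite | Success route by day 30 | Follow-up to primary endpoint | Survivor count (Sample Size) |
|---|---|---|---|---|
| A. Removed for recovery day 10; device-related stroke day 12; alive day 30 | Event-free (event came after support) | Met | Closed day 10 | Survivor |
| B. Removed for recovery day 10; unplanned renewed support day 12; alive day 30 | Event-free | Met | Closed day 10 | Survivor |
| C. Removed for recovery day 10; dies day 12 | Event-free if the window also governs survival; failure if it governs only adverse events | Met | Closed day 10 | Non-survivor |
| D. Alive, event-free, on device at day 30 | Met so far | Not met | Closed day 30 | Survivor |
| E. As D, device-related stroke day 38 | Failed (support continues, no cap) | Not met | Event falls after the endpoint | Survivor |

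A and B are successes under every definition. C is contradictory. D meets the composite without meeting a success route. E fails the composite, but the event lies outside the period that the schedule section sets.

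**Is day-30 survival observed?** Planned observation after removal on day d ends at day d + 7. It reaches day 30 only if d + 7 ≥ 30, that is d ≥ 23. For anyone removed before about day 23, the stated follow-up does not secure the vital status that the Sample Size rule needs.

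**Size.** One patient is 1/9 = 11.1 percentage points. For A and B, adding the 7 days can only remove successes, so the direction is known. The amount is not, because the article gives no rate of failure after removal.

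**The case against.** The best defence is that counting device-related events while the device is in place is a reasonable choice for a temporary bridge in an exploratory, first-in-human study with descriptive analysis. Exchange for transplant bridging is an intended outcome, serious adverse events go to the safety board in any case, and a journal article may leave detailed windows to the full protocol. The choice is indeed defensible, and planned exchange should remain a success. But the article does more than omit detail: it fixes a window, and its other sections do not agree with that window. Reporting to the safety board does not alter the endpoint.

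Several stronger readings are tempting and not supported.

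- A reader might infer that a patient who dies just after removal is plainly a success. The survivor count in Sample Size makes a death before day 30 a failure, and the support-period limit may apply only to the adverse events. For death this is a contradiction.
- A reader might infer that all follow-up stops at day 30. Only follow-up to the primary endpoint does; the schedule continues.
- A reader might infer that a day-38 event necessarily changes a patient's result. Both success routes end at day 30, so this depends on how a patient still supported on day 30 is classified, which is unstated.
- A reader might take the column for 7 days after removal in Table 2, which appears empty, as proof that nothing is collected. The table may have lost cells when the text was extracted, so no weight rests on it.
- A reader might attach a loss of power. If 5%, 10% or 20% of recorded successes failed after removal, a 90% rate would become 85.5%, 81% or 72%, and the chance of at least eight of nine would fall from 0.775 to 0.617, 0.467 or 0.234. The arithmetic is right, but the rates are assumed and the cut-off belongs to survival, so these are not chances of passing any rule in the protocol.

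**Conclusion.** The point holds as a defect in the endpoint definition. As written, a recovery that fails through a device-related event or unplanned renewed support within the planned 7 days is scored as a success. Death after removal but before day 30 is scored differently in different sections. Patients still supported at day 30 have no settled classification.

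Each affected patient is worth 11 percentage points of nine. How many will be affected cannot be estimated from the documents, and no claim is made about when complications usually appear after removal. The conclusion rests on the wording alone. The one assumption is that the article's endpoint text reflects the full protocol.

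**What to change.** In Study Objectives and Endpoints:

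1. Count deaths and device-related serious events and complications from implantation to 7 days after removal, or to day 30 for patients still on the device.
2. Score removal for recovery as success only if the patient is alive without unplanned renewed mechanical support at the planned 7-day visit. Keep planned exchange for transplant bridging as a success route.
3. State how a patient still supported at day 30 is classified, and report later on-device events separately as safety data.

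Record vital status at day 30 for every patient, since the 7-day period does not reach it after early removal. Then align Sample Size, Study Objectives and Endpoints, and Patient Enrollment and Study Schedule, saying which quantity the decision rule counts.

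Four patients had been enrolled in this open-label study by the end of January 2018. The change should therefore be dated, and results should also be reported under the endpoint as the protocol now words it, so that readers can see whether the change altered the result.

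The cost is a dated amendment, a day-30 vital-status check and possibly a slightly lower success rate. The 7-day follow-up is already planned.

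### The hypothesis, sample size and success rule are set on 30-day survival, but the primary endpoint is a different composite with no P0, P1 or cut-off of its own

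*Protocol article*

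**What the plan says.** **Sample Size.** "A total of nine patients will be enrolled in the study", under a Simon minimax two-stage design. "The hypothesis to be tested was H0: P < P0 vs H1: P > P1", "where P is the probability of mortality at 30 days", with P0 = 50%, P1 = 90% and false-positive and false-negative rates of at most 10% each. Stage 1 has four patients and stops if no more than two survive. The final rule is "declaring success if more than seven patients survive" out of nine. The rules count survivors, so P works only as 30-day survival, although it is printed as mortality.

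**Study Objectives and Endpoints.** "The primary endpoint is a composite of survival free of device-related serious adverse events and complications during device support". For left-sided support, success is removal of the device after cardiac recovery, or exchange to another VAD as a bridge to transplantation, within 30 days. For right-sided support, only removal after recovery counts.

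**Statistical Analysis.** Safety and efficacy endpoints are described, with exact two-sided 95% Clopper-Pearson intervals for binary ones. This section gives no threshold or test for the composite and does not refer back to the two-stage rule.

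**The concern.** The protocol fixes a formal test and a formal primary endpoint, and they concern different variables. A patient can be classified differently by each:

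- A survivor with a device-related serious adverse event counts towards success in Sample Size but does not meet the composite.
- A patient alive at day 30 and still on the device counts as a survivor but is not among the listed successes. The data-collection table has visits every two weeks after day 30, so such patients are foreseen.
- A patient removed from the device event-free who dies before day 30 is not a 30-day survivor, but could be a composite success because the composite runs only during support.

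The primary objective is safety and effectiveness in a first-in-human study, yet the rule for declaring success has no device-safety component. The stated error rates describe a conclusion about survival, not about the primary endpoint.

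**Working it through.** **Inputs from Sample Size:** n1 = 4, stop if 2 or fewer; n = 9; success if more than 7; P0 = 0.50, P1 = 0.90; both error rates at most 10%.

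**Formula.** With X ~ Bin(4, p) in stage 1 and Y ~ Bin(5, p) in stage 2, and success needing at least s of nine:

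Pr(success) = Pr(X = 3) × Pr(Y ≥ s − 3) + Pr(X = 4) × Pr(Y ≥ s − 4)

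**Step 1. The plan's own figure.** A search over all two-stage designs with these parameters gives a smallest n of 9, with n1 = 4, stop at 2 or fewer, and success at 7 or more. So N = 9 and the stage 1 rule reproduce.

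- s = 7, p = 0.9: 0.2916 × 0.91854 + 0.6561 × 0.99144 = 0.918
- s = 7, p = 0.5: 0.25 × 0.1875 + 0.0625 × 0.5 = 0.078
- s = 8 (as printed), p = 0.9: 0.2916 × 0.59049 + 0.6561 × 0.91854 = 0.775
- s = 8, p = 0.5: 0.25 × 0.03125 + 0.0625 × 0.1875 = 0.020

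The printed boundary misses the stated false-negative rate even for survival. That is a separate error, so both boundaries are carried below.

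**Step 2. Success declared on survivors when the composite is poor.** The protocol gives no composite rate. Assume 90% survival and a composite rate of 50%, the value P0 would take if applied to the composite. From step 1:

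| Boundary | Rule counts survivors (90%) | Same rule counts composite successes (50%) |
|---|---|---|
| more than 7 | 77.5% | 2.0% |
| 7 or more | 91.8% | 7.8% |

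**Step 3. Power if the cut-offs were moved to the composite.** Assume 90% survival and a share q of survivors who also meet the composite, so the composite rate is 0.90 × q:

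| q | Composite rate | more than 7 | 7 or more |
|---|---|---|---|
| 1.0 | 90% | 77.5% | 91.8% |
| 0.9 | 81% | 46.7% | 71.5% |
| 0.8 | 72% | 23.4% | 47.0% |
| 0.7 | 63% | 9.8% | 26.0% |

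In this model every composite success is a survivor, so the chance that the survivor rule succeeds while the composite rule does not is a difference. At a 72% composite rate it is 77.5 − 23.4 = 54.1% (more than 7) or 91.8 − 47.0 = 44.8% (7 or more).

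**Step 4. Sample size for the composite.** With P0 = 50% and both errors at most 10%, the minimax N is 9 for P1 = 90%, 12 for P1 = 85% (type I error 7.3%, power 90.8%) and 16 for P1 = 80% (9.9%, 90.5%).

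**The case against.** The best defence is that the study is labelled exploratory. The composite will be reported with an exact interval, an independent board reviews all serious adverse events, and enrolment is held after the fourth patient for a 7-day safety review. Device-related harm would not go unseen. This all stands, but it does not remove the contradiction: the protocol itself states a hypothesis, error rates and a rule for declaring success, and none of them uses the primary endpoint. Nor is this a matter left to the SAP, because the protocol fixes both sides.

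Some stronger readings are tempting and should not be drawn:

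- A reader might infer that the composite rate can never exceed the survival rate. The two are not strictly nested, as the patient who dies after event-free removal shows. The composite is probably harder to meet, but the text does not guarantee it.
- A reader might set the 10–47% power under the printed boundary against the planned 90%. That mixes in the boundary error. The like-for-like reference is 77.5% for more than seven, and 91.8% for seven or more.
- A reader might say that a trial with many survivors and many device events fails its primary endpoint. The protocol sets no threshold for failing it; the defect is that the endpoint is not tested at all.
- A reader might think that renaming 30-day survival as primary costs nothing. Patient Enrollment and Study Schedule follows patients for only 7 days after removal. A patient explanted on day 5 is followed to about day 12, so day-30 status is not assured.

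**Conclusion.** The point holds and should be corrected before the results are analysed. The hypothesis, P0/P1, the stage 1 stop and the success rule use 30-day survival, the primary endpoint is another variable, and nothing in the protocol connects them. Success can be declared without testing the primary endpoint, and the stated error rates do not cover it.

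The size depends on rates the protocol does not give. Under 90% survival and a 50% composite rate, the survivor rule succeeds 77.5% or 91.8% of the time, against 2.0% or 7.8% for the same rule on the composite. At composite rates of 63–81%, power on the composite is 10–47% (more than seven) or 26–71% (seven or more). The 63–81% range rests on an assumed 70–90% of survivors meeting the composite. If a composite P1 of 90% were justified, nine patients would serve with the boundary at seven or more, but the protocol does not make that claim. Printing P as mortality and the boundary as more than seven are separate errors; this finding stands without them.

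**What to change.** Define P as the per-patient probability of primary-endpoint success. Count those successes in the hypothesis and the final rule. Either count them in stage 1 as well, or state that stage 1 is a survival-only safety look. State and justify P0 and P1 for the composite, and give power at nine patients over a range of composite rates, as in step 3.

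If stage 1 stays on survival, the composite's type I error at P0 = 50% with seven or more of nine cannot exceed the single-stage value of 9.0%, because early stopping can only reduce the chance of declaring success.

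**Cost.** An amendment and a less favourable power statement, unless a composite P1 of 90% is justified. Keeping nine patients means accepting that lower power; keeping 10% errors against P0 = 50% would take 12 patients at P1 = 85% or 16 at P1 = 80%. By the end of January 2018 four patients, the size of stage 1, were already enrolled in an open-label trial. The change must therefore be dated and made without reference to their outcomes.

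**Alternative.** Make 30-day survival primary and the composite a key secondary endpoint. This also resolves the conflict, but needs vital status at day 30 for patients explanted early.
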